## Abstract

**Background:**

Although most clinical guidelines throughout the world indicate that clinicians take two bitewings for detecting caries lesions in primary molars of all children, evidence for this recommendation is essentially based on cross-sectional studies performed in laboratory settings or using convenience samples. The benefits and impact of performing radiographs on diagnosis and treatment decision of caries lesions in primary teeth, mainly considering relevant outcomes for patients, have not been evaluated yet. Thus, the aim of this randomized clinical trial will be to evaluate the impact of performing radiographic examination adjunct to the visual inspection for detecting and making treatment decision regarding caries lesions in primary teeth compared with visual inspection performed alone. We will consider different outcomes related to children's health and welfare.

**Methods/Design:**

To reach this objective, 250 children ages 3 to 6 years who sought dental treatment in our dental school will be randomly allocated in two groups according to the diagnostic strategy used for caries detection: visual inspection performed alone or visual inspection associated to radiographic examination. Two trained and calibrated examiners will carry out the examinations and elaborate the treatment decision plan. Then, children will be treated and followed up for 2 years, with evaluations after 12 and 24 months after the inclusion of children in the study. Children will also return after 6 and 18 months to reinforce the preventive orientations. Primary outcome will be the number of dental surfaces in need of dental treatment at the follow-up. Secondary outcomes will be the components of the primary outcome separately, as well as, proportion of false-positive results, the oral health-related quality of life, cost-efficacy, cost-adjusted life years, and number of new lesions in the first permanent molars.

**Discussion:**

Our working hypothesis is that radiographic examination would actually exert little influence on patient-centered outcomes, and visual inspection would be enough as diagnostic strategy for caries detection in primary teeth.

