#### Sample size

The sample size calculation was based on the occurrence of the primary outcome: number of dental surfaces of primary molars with operative needs during the follow-ups and the incidence data. Considering operative needs, we observed a mean of 17.6 surfaces with new caries lesions after 2 years [31], approximately 10 % restoration failure of occlusal or occluso-proximal restorations in 2 years [32], 0.08 extracted teeth in 2 years, with 0.2 surfaces [33] and 0.3 pain episodes in 2 years, with one surface [33].

Therefore, a mean of 19 surfaces with treatment need in the visual inspection alone group is expected. A difference of five surfaces with treatment need in the visual plus radiographic method group was considered as a minimally clinically important difference. The standard deviation values expected for visual and visual plus radiographic groups were 15 and 10, respectively. Therefore, using a two-tailed test and considering a significance level of 5 % and 80 % power, the minimum sample size of children calculated was 103 per group. Anticipating an attrition rate of 80 %, the final minimum sample size was 250 children for the entire study.

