#### Statistical methods

For comparing the outcomes between the two groups, Student’s *t* test and Poisson regression analysis will be performed. With regard to the impact of Oral Health on quality of life, differences in the final and baseline scores will be compared between the groups through Student’s *t* test or the Mann–Whitney test, depending on the normality of the data distribution.

Multivariate analysis will be conducted to investigate the influence of the radiographic examination on treatment decision. Time and treatment cost will be compared by Student’s *t* test. An incremental cost-efficacy ratio will be used to compare the economic impact of both diagnostic strategies, considering both the initial examination and possible treatment and re-treatments during the study. The quality-adjusted life year (QUALY) will be also calculated in order to estimate the ratio of cost saved/spent by the use of the proposed diagnostic strategy. For all analyses, the level of significance will be set at 5 %.

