Until now, however, no randomized clinical trial was conducted to evaluate caries diagnosis strategies. With the expected results, we aim to achieve the refutation of the recommendation to conduct bitewing radiographs for detecting caries lesions, even in children without signs or symptoms, which is present in all protocols of clinical procedures worldwide. On the other hand, in case of favorable results obtained with the experimental group, we will confirm the benefits of strategies of caries detection advised by those clinical guidelines. To the best of our knowledge, this is the first randomized clinical trial to evaluate diagnostic strategies for diseases related to the oral cavity, considering the whole playing field of dentistry.

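### The Discussion looks to conclude that visual inspection suffices and that the bitewing advice is refuted, but only a two-tailed difference test is planned, and a non-significant result would not support that conclusion

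*Protocol article*

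**What the plan says.** The Discussion paragraph of the abstract gives the working hypothesis: radiographs are expected to make little difference to the outcomes that matter to patients, and "visual inspection would be enough as diagnostic strategy for caries detection in primary teeth". The main Discussion carries this into a policy conclusion. On the strength of the results the investigators expect, it says "we aim to achieve the refutation of the recommendation to conduct bitewing radiographs for detecting caries lesions". The alternative it names is that "in case of favorable results obtained with the experimental group, we will confirm the benefits of strategies of caries detection". It describes no third, inconclusive outcome.

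The Sample size section assumes a mean of 19 surfaces needing treatment with visual inspection alone and standard deviations of 15 and 10, and says "A difference of five surfaces with treatment need in the visual plus radiographic method group was considered as a minimally clinically important difference". The test is two-tailed, "considering a significance level of 5 % and 80 % power", which leads to 103 children per group. The Statistical methods section names Student's t test and Poisson regression for comparing the groups, at the 5% level throughout.

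No section describes a non-inferiority or equivalence objective, calls the 5 surfaces a margin, or says how a confidence interval will be used. The formal aim, in the abstract's Background and under Objective, is neutral: to evaluate the effect of adding radiographs to visual inspection.

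**The concern.** The hypothesis is one of little or no difference, and the conclusion sought is that an existing recommendation should fall. Supporting that takes evidence that any disadvantage of visual inspection alone is smaller than an important amount. A difference test does not provide it: failing to reject equality is compatible with equality, but also with a disadvantage the plan itself calls important.

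The result most in keeping with the hypothesis is a small, non-significant difference. For that result the protocol has no rule separating the case where an important disadvantage has been excluded from the case where it has not. At stake is the headline conclusion on the primary outcome. A claim to overturn widely used guidance could rest on a result that leaves the question open, and a rule chosen after the groups had been compared would carry little weight.

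**Working it through.** **Inputs** (Sample size and Statistical methods sections): difference 5 surfaces; standard deviations 15 (visual alone) and 10 (visual plus radiograph); two-sided 5%; power 80%; 103 per group. All results below take 103 evaluable children per arm and use the normal approximation. D is the mean for visual alone minus the mean for visual plus radiograph, so a positive D favours radiographs.

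**1. The plan's own figure.** n = (1.960 + 0.842)² × (15² + 10²) / 5² = 7.849 × 325 / 25 = 102.04, rounded up to 103 per group. The stated number reproduces as a two-sided test for a difference.

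**2. Precision.** SE = √(325/103) = 1.776. The half-width of the 95% interval is 1.96 × 1.776 = 3.48 surfaces.

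**3. Where non-significance and exclusion of 5 part company.**
- Non-significant in favour of radiographs: observed D below 3.48.
- Upper limit below 5: observed D below 5 − 3.48 = 1.52.
- For observed D between about 1.5 and 3.5, the test is non-significant and 5 is not excluded. At the top of that band the upper limit is 3.48 + 3.48 = 6.96.

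**4. How often each happens.** P(non-significant) = Φ(1.96 − D/SE) − Φ(−1.96 − D/SE). P(upper limit below 5) = Φ((5 − D)/SE − 1.96). For D of 0 or more, the last column is P(observed D between 1.52 and 3.48).

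| True D | Non-significant | Upper limit below 5 | Non-significant, 5 not excluded |
|---|---|---|---|
| 0 | 95% | 80% | 17% |
| 3 | 61% | 20% | 40% |
| 4 | 39% | 8% | 30% |
| 5 | 20% | 2.5% | 17% |

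**5. Power to exclude 5 at a true difference of 0.**
- Standard deviations 15 and 10: Φ(5/1.776 − 1.96) = Φ(0.855) = 80%.
- Both standard deviations 15: SE = √(450/103) = 2.090; Φ(5/2.090 − 1.96) = Φ(0.432) = 67%. The half-width becomes 4.1 surfaces.

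**6. Dependence on the margin.** The documents state no margin, so values other than 5 are assumptions, shown only for range. Per-arm size for 80% power at a true difference of 0, with standard deviations 15 and 10, is 7.849 × 325 / margin²: 103 for a margin of 5, 160 for 4, 284 for 3 and 409 for 2.5.

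**The case against.** The strongest reply is that the stated objective is neutral and a two-tailed test suits it. The statements about sufficiency and refutation are Discussion prose, not a decision rule. Three stronger readings are tempting, and the documents do not bear them out.

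- *A reader might infer that the investigators have committed to reading a non-significant p-value as proof that visual inspection is enough.* No section says so. Statistical methods lists tests and is silent on how a null result will be read. A significant result favouring visual inspection alone would be a valid route to the refutation, and the Background, with its concern about false positives and unnecessary operative treatment, makes that possible. False positives, quality of life and cost are compared as well.
- *A reader might infer that non-significance is likely when radiographs bring a nearly important benefit.* At a true benefit of 4 surfaces the chance is 39%. It passes one half only below about 3.5 surfaces. The 20% at 5 surfaces is the type II error the plan accepted. Benefits of 3 or 4 surfaces also lie below the plan's own threshold, so they cannot count as serious misses under a rule that tolerates anything below 5.
- *A reader might infer that the trial is too small for the question.* Under the stated standard deviations, 103 per arm gives about 80% power to exclude 5.

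It can also be said that interpreting a null result is a matter for an analysis plan, which is not shown. That would answer a mere omission. Here the article states the conclusion sought, the sample-size basis and the tests, and the last two do not lead to the first when the result is null. That much of the point stands.

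**Conclusion.** The point holds as a mismatch between the conclusion sought and the test planned. It is confined to a non-significant primary result, which is what a hypothesis of little influence would most naturally produce. Such a result would not by itself show that visual inspection suffices. In the band of observed differences from about 1.5 to 3.5 surfaces, it leaves the plan's own important difference inside the interval. That occurs in about 17% of trials when there is no true difference and about 40% when the true difference is 3.

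These figures rest on 103 evaluable children per arm, standard deviations of 15 and 10, and 5 surfaces as the threshold. The unequal standard deviations go with an assumed effect of radiographs. If radiographs make little difference, more nearly equal values are plausible, and power falls towards 67% if both are 15. The 5 surfaces are 26% of the expected 19 (5/19), and the protocol offers them only as the difference to detect, so their use as a margin needs its own justification. Objective, randomisation, outcome and sample-size arithmetic are not called into question by this point.

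**What to change.** Before unblinding, prespecify that the primary result is interpreted from the two-sided 95% confidence interval for the mean difference (visual alone minus visual plus radiograph) against 5 surfaces, with a short justification of 5 as the margin. Name the mean difference as the deciding scale, because Poisson regression is also planned and estimates a ratio. The readings would be:

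- Upper limit below 5: visual inspection alone is not importantly worse.
- Lower limit above 0: radiographs reduce treatment need.
- Both of these: radiographs bring a benefit smaller than the important difference.
- Upper limit below 0: visual inspection alone is better.
- Neither of the first two: inconclusive.

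Reword the abstract's Discussion paragraph and the main Discussion so that non-significance alone is not taken as refutation. State in the Sample size section that power for the first reading at a true difference of 0 is about 80% with standard deviations of 15 and 10, and about 67% if both are 15.

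The cost is wording in the hypothesis, sample-size and analysis text, with no added recruitment under the stated standard deviations. The article reports recruitment as ongoing, with 225 children included and no results, so on its account the rule can still be set in advance. The downside is a stricter bar for the conclusion the investigators expect: some results they might have presented as support would have to be reported as inconclusive.

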**Trial registration:**

NCT02078453. Registered 4 March 2015.

**Electronic supplementary material:**

The online version of this article (doi:10.1186/s13063-016-1196-5) contains supplementary material, which is available to authorized users.

## Background

### Background

Visual inspection is a quick and easy method for caries lesions detection in primary teeth [1]. Moreover, the method has presented high specificity [2], and it is the unique method validated to assess caries lesions activity [3, 4]. For those reasons, it is routinely used in daily clinical practice [1].

Nevertheless, the method has not presented high sensitivity in detecting caries lesions, mainly at proximal surfaces [2]. To overcome this limitation of the visual inspection, many clinical guidelines used throughout the world have advised that dentists take two bilateral bitewing radiographs in children to detect missed caries lesions in primary molars [5–7]. The radiographic method is capable of increasing the sensitivity of visual inspection in primary teeth, decreasing the number of false-negative results in occlusal [2] and proximal surfaces [2, 8].

However, the increase in the sensitivity usually occurs with the expense of a higher number of false-positive results. Considering the dental caries, this increase of false positives may not be good for two main reasons:The prevalence of non-evident caries lesions seems to be low in most populations. Thus, there would be a higher number or diagnostic errors using methods with low specificity than with low sensitivity;A false-positive result would lead to an unnecessary operative treatment, whereas a false-negative result could be followed up and detected further with no consequences for the patient.

In addition, performing unnecessary operative treatment seems to be more costly than missing some caries lesions undetected by visual inspection alone [9].

Some studies have observed this trend of an increased number of false-positive results with the radiographic method [10–13]. However, most of these studies considered the criterion validity of the methods; hence, they compared the results of the methods with the results obtained with a reference standard method. This type of research usually obtained the rate or correct diagnosis of the method, but it is not concerned with the benefits for the patients.

No study performed to evaluate caries diagnosis strategies has ever evaluated important outcomes for the patients. A correct diagnosis is not necessarily a benefit for the patient. For instance, the detection of a caries lesion in a primary tooth near its exfoliation is not good for the patient because it would lead to unnecessary operative treatment. Therefore, studies that evaluate the benefits for the patients are essential to evaluate the actual utility of radiographic method to detect caries lesions in primary teeth. This reason motivates the realization of the present study.

### Objective

The aim of the present protocol will be to evaluate the effect of caries lesions detection in primary teeth performed with the radiographic examination adjunct to the visual inspection on the occurrence of outcomes related to the oral health of children through a randomized clinical trial.

### Trial design

A randomized controlled clinical trial with two parallel arms will be designed. One group will comprise children who will receive the diagnosis and treatment decision planned with the visual inspection alone. Another group will be formed by children who will receive diagnosis and subsequent dental treatment planning using visual inspection associated with radiographic examination.

## Methods

This article adheres to the guideline for randomized clinical trial protocols (SPIRIT). The SPIRIT checklist is described in the Additional file 1.

### Participants, interventions, and outcomes

#### Setting

The children will be randomly selected from a pool of enrollment forms of children (3 to 6 years old) who sought dental treatment at our school. Because we will select patients who looked for dental treatment, we can consider extrapolating the results to the dental office setting. This context is adequate since clinicians usually apply these diagnostic strategies in the daily clinical practice.

#### Eligibility: inclusion and exclusion criteria

The inclusion criteria will consider the following children:who sought dental treatment in our school;are aged 3 to 6 years old; andhave at least one primary molar in the mouth.

The following will be excluded from the study:children whose parents refuse to participate in the research orchildren who present behavioral problems during the initial appointments.

#### Interventions

An initial clinical examination will be performed to evaluate the teeth present in the mouth, as well as the caries experience using the World Health Organization criteria [14]. The children will be classified in subgroups according to age (3 and 4 years old or 5 and 6 years old) and according to the caries experience (children with decayed-missing-filled-surfaces (dmf-s) less than or equal to 3 or children with dmf-s greater than 3).

If the child is eligible to participate in the study, bitewing radiographs will be taken from each side, including the upper and lower primary molars (two bilateral radiographs for each child), as recommended by different clinical guidelines throughout the world [5–7]. Complementary periapical radiographs also will be taken when necessary. Radiographs will be processed using the time/temperature method, in which the film stays in the revealing solution (Eastman Kodak, Rochester, NY, USA) for 2 min at a temperature of approximately 27 °C [15], followed by a fixation time of 10 min in fixing solution (Eastman Kodak, Rochester, NY, USA), and then by washing in water for 20 min [15]. The revealing and fixing solutions will always be new, replaced at the beginning of each period of clinical appointments, guaranteeing the quality of processing.

In addition, a questionnaire to evaluate the impact of oral health on the quality of life of the children at baseline will be applied for the parents. The instrument used will be the Brazilian version of the Early Childhood Oral Health Impact Scale (ECOHIS) [16, 17]. Then, the participant will be randomly allocated in one of the two groups.

The groups will be defined according to the diagnostic strategy used for reaching the treatment decision related to dental caries in primary molars proposed for each child. The two groups are as follows:Visual inspection alone: The treatment decision plan will be based only on a visual inspection. The examiners will not receive the bitewings of these children to elaborate the treatment plan. They will only access periapical radiographs when necessary (to decide between endodontics or tooth extraction, for example); those radiographs will be available after the decision regarding the process for the other teeth has been rendered.Visual inspection plus radiographic: The treatment plan will be based on the visual inspection complemented by radiographic examination. The access to periapical radiographs is also permitted in this case.

At the second clinical appointment, two different examiners will perform the examination and elaboration of the treatment plan. They will be trained and calibrated prior to the study. During the study, their calibration will also be checked after each 50 children included in the study.

#### Caries detection procedures

The visual inspection will be done according to the International Caries Detection and Assessment System (ICDAS) [18]. The children will be positioned in a dental chair, under illumination, and they will receive prophylaxis using rotating bristle brush and a pumice/water slurry. The examiners will use a dental mirror and a ball-ended probe for the examination. The teeth will be examined wet, and then, they will be air-dried for 5 s with a 3-in-1 syringe. The examiner will also evaluate the caries activity status if a caries lesion is present [19]. The condition and treatment decision of each dental surface will be recorded on an appropriate form.

In all cases, the clinical evaluation will be performed without knowledge of the experimental group of the participant. After the examination, the examiner will be informed of the enrollment group and will plan the treatment with or without access to the bitewing radiographs.

For the children allocated to the experimental group, the same examination procedure will be done, but a visual inspection and radiographic examination will be used to reach the treatment decision. Radiographic evaluation will be performed using a light box.

The treatment plan elaborated according to the allocated group will be put in envelops that will be delivered for the dentists responsible for performing the dental treatment. On the first day of treatment, the children will receive orientation for oral hygiene and dietary advice, and an anamnesis will be performed with the parents of the children. Dentists will perform the dental treatment following the plan and according to the predetermined protocols for each type of treatment.

#### Dental treatment protocols

The choice of the protocols of treatment is based on the best available evidence:Operatory treatments will be done with partial caries removal [20].High-viscosity glass ionomer cement will be used to restore cavitated active caries lesions in occlusal [21] or approximal [22] surfaces (score 4 of ICDAS or higher and/or lesions reaching the outer half of the dentin in the radiographic image).Resin-modified glass-ionomer cement will be used for restorations of lesions involving more than two surfaces [23].Non-cavitated active caries lesions will be treated with fluoride varnish [24].Prevention measure orientation will be based on the orientation of oral hygiene using fluoride dentifrice with 1000 to 1500 ppm of fluoride [25] and dietary advice [26].Endodontic treatment will use iodoform paste [27, 28].Dental extractions and other types of treatment will be provided.

The dentists responsible for the treatments will not receive the bitewings radiographs of the participants; they will only have access to periapical radiographs that may be useful for indirect pulp capping, endodontic treatment, and extraction.

During the operatory interventions, the presence of soft or hard carious tissue or the absence of carious tissue will be evaluated in order to record possible false-positive diagnosis for dentine caries.

The time required for all procedures and the materials used will be registered by an external examiner for the economic analysis. The time spent for each procedure, including return visits, will be considered in calculations of the direct and indirect costs.

The number of visits of each participant and the procedure done at each session, with their respective duration times, also will be recorded. For the calculation of direct costs, we will consider the average of market prices of the materials used in each procedure [29, 30]. Such values will be obtained by averaging the prices from different sources for the products being used, and these numbers will be updated during the study. For the calculations, indirect costs will be also considered, as described in previous studies [29, 30].

